# The effect of ‘sleep high and train low’ on weight loss in overweight Chinese adolescents: study protocol for a randomized controlled trial

**DOI:** 10.1186/1745-6215-15-250

**Published:** 2014-06-25

**Keywords:** Hypoxia, Living high-training low, Weight loss, Adolescents, Gastrointestinal hormone

## Abstract

**Background:**

Exercise and diet are the cornerstones for the treatment of obesity in obese children and adolescents. However, compensatory changes in appetite and energy expenditure elicited by exercise and dieting make it hard to maintain a reduced weight over the longterm. The anorexic effect of hypoxia can be potentially utilized to counteract this compensatory increase, thereby enhancing the success of weight loss. The purpose of the study is to assess the effectiveness of four week intermittent hypoxia exposure added to a traditional exercise and diet intervention on inducing short- and longterm weight loss in obese adolescents.

**Methods/Design:**

In this randomized parallel group controlled clinical trial, 40 obese adolescents (20 boys and 20 girls, 11 to 15-years-old), will be recruited from a summer weight loss camp at the Shanghai University of Sport, China. Participants will be stratified by gender and randomly assigned to either the control group or the hypoxia group. During the four-week intervention period, both groups will exercise and eat a balanced diet. Additionally, the control group will sleep in normal conditions, while the hypoxia group will sleep in a normobaric hypoxia chamber (sleep high and train low). The primary outcome will be body composition and the main secondary outcomes will be the circulating levels of appetite regulatory gastrointestinal hormones. All the outcome measures will be assessed at baseline, after the four-week intervention, and at two months follow-up.

**Discussion:**

Our study will be the first to evaluate the effectiveness of ‘sleep high and train low’ on short- and longterm weight loss among obese adolescents. A potential mechanism for the appetite regulatory effect of hypoxia will also be explored. The results of the study will provide an evidence-based recommendation for the use of hypoxia in a weight loss intervention among obese children and adolescents. Furthermore, the clarification of mechanisms leading to weight loss in ‘sleep high and train low’ might provide information for the development of new strategies in combating obesity.

**Trial registration:**

This trial was registered on 10 January 2014 at the Chinese Clinical Trial Registry with the registration number: ChiCTR-TRC-14004106.

## Background

Obesity is a global pandemic and its prevalence among children and adolescents has also increased worldwide, becoming a serious public health problem [1]. In China, nearly 215 million people are overweight or obese, and 12% of these are children (< 17-years-old), as estimated by the 2002 China National Nutrition and Health Survey [2]. Obesity in childhood has been associated with an increased risk of diabetes, hypertension, cardiovascular disease and various cancers in adulthood [3,4]. Therefore, preventing and treating obesity in children and adolescents is crucial.

The causes of childhood obesity are complex and multifaceted involving genetic factors, environmental, and behavioral factors. The current worldwide epidemic of obesity is believed to be attributable to the modern living environment which promotes a sedentary lifestyle and excessive consumption of calorie-dense food. Accordingly, a lifestyle modification including a healthy diet and increased physical activity has been recommended as the cornerstone of prevention and treatment of obesity. Physical activity increases energy expenditure and, in combination with a healthy diet, is effective in inducing weight loss. However, the reduced weight achieved through weight loss programs is hard to maintain over the longterm. The failure to achieve longterm weight loss is believed to be caused by compensatory changes in appetite and energy expenditure elicited by exercise and dieting. Currently, a complete understanding of the relationship between exercise, appetite regulation, and weight management is lacking.

Recent research has revealed that appetite-regulating hormones might play an important role in moderating the interrelationship between exercise and dieting, appetite, and weight regain. Among various potential appetite-regulating hormones, the gastrointestinal hormones, ghrelin, peptide YY (PYY), cholecystokinin (CCK) and glucagon-like peptide-1 (GLP-1) are well studied. Ghrelin is the only hormone that has been shown to be orexigenic, while PYY, CCK, and GLP-1 are satiety regulatory hormones [5,6]. These hormones are episodic hormonal signals occurring in unison with episodes of eating. They signal satiation and satiety either via the vagus nerve (which connects the gut to the brain) or via blood perfusing the hypothalamus.

It is accepted that in response to weight loss, counter-regulatory adaptations develop in the appetite regulatory system, including the gastrointestinal hormones, defending impositions that promote a negative energy balance. Different weight loss intervention approaches are likely to cause different counter-regulatory adaptations in terms of the content and the magnitude of the response. There is some evidence suggesting that diet-induced weight loss is associated with a compensatory increase in total ghrelin (GT) plasma levels and a blunted postprandial release of PYY and GLP-1 [7,8]. Exercise-induced weight loss may increase the drive to eat, as shown by increased levels of acylated ghrelin (AG) and subjective feelings of hunger in fasting, but it may also improve satiety as evidenced by an increase in the late postprandial release of GLP-1 after exercise training [9].

Few studies have investigated the combined effect of exercise and dieting on appetite in children and adolescents. Based on the limited data, it appears that ghrelin levels increase after a weight reduction program, with no change in PYY levels [10-13]. Similarly, we have observed an increase in ghrelin concentrations after weight loss in adolescents who participated in an exercise and diet intervention for four weeks in a summer camp program in a previous study (unpublished data).

Recently, the effect of high altitude on appetite regulation has attracted researchers’ interest. It is a widely observed phenomenon that a high altitude can induce loss of appetite [14-16]. In many studies, loss of appetite and the resulting decrease in energy intake have been attributed to acute mountain sickness (AMS), symptoms of which include headache and anorexia. However, loss of appetite cannot merely be a by-product of AMS because anorexia and weight loss still persist when symptoms of AMS have subsided [17]. Furthermore, studies conducted in normobaric hypoxia chambers, where other environmental stressors associated with high altitude are eliminated (extreme cold and physical exertion), have demonstrated that hypoxia *per se* can cause reduced appetite and energy intake, and loss of body weight [18]. It has been suggested that the effect of hypoxia on appetite is mediated by the changes in gastrointestinal hormones [19-22].

It is perceivable that to promote success in longterm weight loss, hypoxia can be implemented in a traditional diet and exercise weight loss program, because the negative effect of hypoxia on appetite might be able to balance the positive effect of diet and exercise. Exercise and hypoxia have been used in combination in sports to induce maximal increase in aerobic endurance in athletes, but have rarely been used in weight loss, especially in children and adolescents. We have run several sessions of weight loss summer camps designed for obese adolescents in Shanghai, China. The effect of exercise and hypoxia on weight loss has been explored in our preliminary studies and interesting results have been generated [23,24]. As such, we are now designing a randomly controlled trial to systematically investigate the longterm weight loss effect of exercise with hypoxia in obese adolescents and determine the mediating effect of the gastrointestinal hormones. We hypothesize that: 1) exercise and hypoxia will have an additive effect on weight loss via increasing energy expenditure and suppressing appetite; 2) hypoxia use will lead to less rebound of weight loss after intervention due to its potential negating effects on compensatory changes in appetite elicited by exercise and diet in a traditional weight loss program; and 3) changes in gastrointestinal hormones (including ghrelin, PYY, CCK, and GLP-1), as well as in cytokine interleukin (IL)-6, will be associated with changes in body weight after the intervention and during follow-up.

### Aims

The aims of this randomized controlled trial (RCT) are to evaluate the effectiveness of intermittent hypoxia and exercise, in combination with a balanced diet, on inducing short- and longterm fat loss in Chinese children and adolescents, and to determine the molecular mechanisms behind the benefits of hypoxia in enhancing weight loss.

## Methods/Design

### Design

This study is a randomized controlled clinical trial with two parallel arms involving 40 obese adolescents. To assess the effectiveness of four weeks of intermittent hypoxia added to a traditional exercise and diet intervention on inducing short (after the four-week intervention) and longterm (at two months follow-up) weight loss in obese adolescents, we will recruit 20 adolescent boys and 20 adolescent girls (aged 11 to 15 years) from our summer weight loss camp. They will be stratified according to gender and randomly assigned to two groups: the control group who will exercise, eat a balanced diet, and sleep in a normobaric condition, and the hypoxia group, who will exercise, eat a balanced diet, and sleep in normobaric hypoxia chambers (‘sleep high and train low’). Outcome assessment and data analysis will be performed by trained professionals who will be blinded to the group assignment of subjects. The flow of participants through the trial is shown in Figure 1.

**Figure 1 F1:**
[figure not shown]
Flow of participants through the trial.

### Sample size estimation

Sample size estimation in this RCT is based on the expected fat loss following four weeks of hypoxia exposure plus exercise and dieting. The data of our preliminary experiment showed that the means of fat percentage decrease in the normoxia and hypoxia groups were 3.1 and 6.0% respectively, and the standard deviation of the change was about 3%. It is estimated that a sample size of 17 participants per group will be required to observe a similar result with a power of 80%. Considering a 15% dropout and exit rate, we will recruit 40 subjects with 20 in each group.

### Ethical approval and consent

The study will be conducted according to the principles expressed in the Declaration of Helsinki. The study protocol has been approved by the institutional review board at the Shanghai University of Sport (reference number: 2014 Ethics Approval Note 1). Participants in this study are volunteers. None of the measurements or the intervention are known to entail any significant health risk. The study has its own physician to ensure the eligibility and safety of all participants. All data will be handled and archived confidentially. The benefits and associated risks of the study will be carefully explained and the voluntary nature of participation will be emphasized. Informed consent and assent will be obtained from all participants and their parents or legal guardians. Participants and their parents or legal guardianswill have the option to end the participation at any stage if they so wish. If the physician and the principal investigator believe that there are risks of serious adverse events in the study the trial will be stopped. The trial is registered with Chinese Clinical Trial Registry as ChiCTR-TRC-14004106.

### Subject recruitment

Obese adolescents aged 11 to 15 years will be recruited from the children registered for the 2014 summer weight loss camp at the Shanghai University of Sport. A public health nurse will assess the Tanner stage of each subject using the Tanner grading system [25,26]. Obesity will be defined based on body-mass index (BMI), calculated as weight in kilograms divided by height in meters squared (kg/m^2^). Although a BMI of ≥ 25 kg/m^2^ and ≥ 30 kg/m^2^ are international cutoff points for overweight and obesity, for many Asian populations individuals with a BMI of ≥ 23 kg/m^2^ are considered to be at increased risk and those with a BMI of ≥ 27.5 kg/m^2^ at high risk [27]. Thus, we chose a BMI of ≥ 25 kg/m^2^ as the criterion to recruit obese adolescents. Adolescents will be excluded if they have concomitant renal, hepatic, or cardiac disease, and/or are being treated with drugs that could affect body weight and appetite (such as orlistat, lorcaserin, and phentermine-topiramate, as well as appetite suppressants).

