### Randomization and blinding

After a participant is confirmed to be eligible and written informed consent has been obtained, she/he will be randomly assigned to the hypoxia or normoxia group. The randomization procedure, stratified according to gender, will be conducted by an independent statistician using a computerized randomization program. In order to minimize the potential bias, the exercise physiologist and the dietitian who manage the exercise training and the diet intervention will be blinded as to whether a subject will sleep in the hypoxia chamber or not. The hypoxia chamber will be prepared by an independent researcher. The researcher performing outcome assessments will be blinded to the subjects’ intervention allocation.

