### Data management and statistical analysis

Data generated in the study will be collected and summarized using mean (standard deviation) values. Group differences in demographical and clinical characteristics at baseline will be tested using a two-sample t-test for quantitative data and chi-square test for qualitative data. Repeated measures analysis of variance (RM ANOVA) will be used to analyze the main effect of treatment and potential time-by-treatment interactions. For these analyses, parametric assumptions of the normality and homoscedasticity will be checked using standard tests and graphical methods. If those assumptions are violated, data transformation and non-parametric procedures will be considered sequentially. Multivariate regression analysis will be performed to analyze the relationship between changes in body composition, appetite score, and gastrointestinal hormones following intervention and during follow-up. Multiple models will be developed and tested for different sets of outcome measures and regressor variables. All statistical analyses will be performed using the Statistical Package for the Social Sciences (SPSS, Inc., Chicago, Illinois, United States) for Windows version 18.0, and a significance level of 0.05 will be used.

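### Tanner stage is graded in every child, but the printed treatment comparison uses neither it nor the stratification factor, gender, giving up some precision and protection against chance pubertal imbalance

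*Protocol article*

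**What the plan says.** All places are in the protocol article.

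- **Who is eligible.** Under Subject recruitment, "Obese adolescents aged 11 to 15 years will be recruited from the children registered for the 2014 summer weight loss camp". Under Design, the target is 20 boys and 20 girls. Entry rests on age and a single BMI cutoff of 25 kg/m². Exclusions are organ disease and drugs that act on weight or appetite. No limit is set on pubertal stage.
- **What is recorded.** Also under Subject recruitment: "A public health nurse will assess the Tanner stage of each subject using the Tanner grading system". This is the only mention of Tanner stage in the article.
- **How children are allocated.** Under Randomization and blinding: "The randomization procedure, stratified according to gender, will be conducted by an independent statistician". No other stratification factor is named.
- **How the arms are compared.** Under Data management and statistical analysis: "Repeated measures analysis of variance (RM ANOVA) will be used to analyze the main effect of treatment and potential time-by-treatment interactions". No covariate is named, not even gender. The same section compares baseline characteristics with t-tests and chi-square tests. It also describes regressions relating changes in body composition, appetite and hormones to one another, with regressors left open.

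**The concern.** The age range runs across puberty in both sexes, and the outcomes (total fat, total lean mass, fat percentage, appetite hormones) may plausibly depend on developmental stage. The trial pays to grade every child and then gives the grade no stated part in the treatment comparison. Gender carries only the part of stage that goes with sex; within each gender stratum of 20, ages still run from 11 to 15. A baseline test can describe an imbalance but does not correct it.

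The model also omits gender, although randomisation was stratified on it. Whatever variance gender and stage explain therefore stays in the error term. With 20 children per arm, an uneven pubertal mix could distort the estimate in this one sample. If it were noticed only after the baseline tests, the decision to adjust would be made with the data in view.

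**Working it through.** **1. The plan's own figure.** Inputs from Sample size estimation: mean fat-percentage decreases of 3.1 and 6.0, so a difference of 2.9; SD of change about 3; power 80%. The significance level is 0.05, taken as two-sided because the article does not say.

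Normal approximation: n = 2 × (1.960 + 0.842)² × 3² / 2.9² = 16.8, so 17 per group. Allowing for dropout: 17 / 0.85 = 20 per group, 40 in total. Both printed figures reproduce, and this point does not affect them. By noncentral t, power at 17 per group is 0.78.

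**2. Chance of a pubertal gap between arms.** Assumptions: each gender stratum of 20 splits 10 and 10 between arms, and 10 of the 20 are late-pubertal. The number of late-pubertal children in one arm is the sum of two independent hypergeometric counts (20 children, 10 late, 10 drawn).

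| Gap in late-pubertal share | Half late-pubertal | 30% late-pubertal |
|---|---|---|
| at least 20 points | 0.35 | 0.31 |
| at least 30 points | 0.12 | 0.09 |

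With half late-pubertal, the mean absolute gap is about 12.6 points.

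**3. Effect of a gap on the change comparison.** Assumption: late and early stages differ by 1 to 2 points in fat-percentage change. Shift = gap × stage difference.

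- Smallest: 0.20 × 1 = 0.2 points, or 0.2 / 2.9 = 7% of the planned effect.
- Largest: 0.30 × 2 = 0.6 points, or 0.6 / 2.9 = 21%.

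The standard error at 17 per group is 3 × √(2/17) = 1.03, so these shifts are about 0.2 to 0.6 of a standard error.

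**4. Effect on the treatment main effect.** Baseline is one of the three visits, so in a repeated measures ANOVA over all three the between-group main effect averages over it. A stable difference in level between stages then enters in full, as gap × level difference. For illustration, if stages differ by 5 kg in lean mass (assumption), a 20-point gap shifts this contrast by 0.20 × 5 = 1 kg with no treatment effect at all. In the time-by-treatment term the same stable difference cancels.

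**5. Gain from adjusting.** For a two-level factor at 50%, the variance explained is 0.25 × (stage difference)² and the total variance is 3² = 9.

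| Stage difference | R-squared | Residual SD = 3√(1 − R²) | Power at 17 per group |
|---|---|---|---|
| none | 0 | 3.00 | 0.78 |
| 1 point | 0.25 × 1 / 9 = 2.8% | 2.96 | 0.79 |
| 2 points | 0.25 × 4 / 9 = 11.1% | 2.83 | 0.83 |

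Powers are noncentral t. Charging two degrees of freedom leaves the 1-point case at 0.79 and takes the 2-point case to 0.82. Any variance explained by gender is not counted.

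**The case against.** The strongest reply has four parts.

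- **Randomisation already deals with chance imbalance.** The unadjusted test is valid and its standard error includes this variability. That stands in full. A reader might infer that the treatment test is biased or its type I error inflated; the design does not support that.
- **Baseline is measured, so stable differences drop out.** This is correct for time-by-treatment, where only a link between stage and change over four weeks to about three months matters. It is not correct for the treatment main effect, which the article also says it will analyse.
- **A large imbalance is not the expected outcome.** This also stands. A reader might infer that a sizeable gap is likely, but at 0.35 for 20 points or more, about 65% of allocations fall short of that. Nor should one quote a large power gain: power of 0.86 would need an R-squared of 20%, hence a stage difference of about 2.7 points, beyond the 1 to 2 assumed here.
- **An analysis plan that is not shown may name covariates.** It may, and the article nowhere rules adjustment out. The point is therefore confined to the model as printed. It does not claim that adjustment will not happen, but recommends a specific improvement to a model the article does state.

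It is also fair that recording a baseline characteristic without stratifying on it is ordinary practice. Nothing here calls for a change to eligibility or stratification.

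**Conclusion.** The point holds as a modest, nearly free improvement to the stated analysis. The printed comparison leaves out both the pubertal grade, which is already collected, and gender, the factor used in randomisation. The loss is in precision and in protection against an unlucky allocation; the validity of the trial and its sample size are not in question.

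Under the stated assumptions the precision at stake is roughly 1 to 5 points of power at 17 per group. There is also about a one-in-three chance of a pubertal gap of 20 points or more, and the shifts calculated for gaps of 20 to 30 points stay below one standard error. The article gives neither the distribution of Tanner stage nor its relation to change in any outcome. The prevalences, stage differences and R-squared values are therefore all assumptions, and the benefit could be smaller or larger. The omission of stage and gender from the printed model rests on the text alone.

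**What to change.** In Data management and statistical analysis, pre-specify baseline Tanner stage (one ordinal term) and gender as covariates in the between-group models for body composition, appetite and hormones. Include each covariate's interaction with time: without it, the terms adjust levels but leave the comparison of change untouched. State that the adjustment applies whatever the baseline tests show.

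The cost is one or two sentences of text, about two degrees of freedom out of roughly 32 to 38, and the assumption that outcomes move linearly with stage, with one slope for boys and girls. No new data are needed, and eligibility and randomisation stay as they are.

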### Randomization and blinding

After a participant is confirmed to be eligible and written informed consent has been obtained, she/he will be randomly assigned to the hypoxia or normoxia group. The randomization procedure, stratified according to gender, will be conducted by an independent statistician using a computerized randomization program. In order to minimize the potential bias, the exercise physiologist and the dietitian who manage the exercise training and the diet intervention will be blinded as to whether a subject will sleep in the hypoxia chamber or not. The hypoxia chamber will be prepared by an independent researcher. The researcher performing outcome assessments will be blinded to the subjects’ intervention allocation.

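### Randomisation is stratified by gender, but the stated treatment analysis names no gender term; if gender is prognostic, the standard error is too large and the test conservative

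*Protocol article*

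**What the plan says.** Gender is the only stratification factor. Design states "we will recruit 20 adolescent boys and 20 adolescent girls (aged 11 to 15 years) from our summer weight loss camp" and continues "They will be stratified according to gender and randomly assigned to two groups". Randomization and blinding repeats this: "The randomization procedure, stratified according to gender, will be conducted by an independent statistician using a computerized randomization program".

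Data management and statistical analysis gives the treatment comparison: "Repeated measures analysis of variance (RM ANOVA) will be used to analyze the main effect of treatment and potential time-by-treatment interactions". No gender factor or stratum term is named there. The only other model in that section is a regression relating changes in body composition, appetite score and hormones to one another, which is not the comparison of arms.

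Sample size estimation compares two mean changes, given as "the means of fat percentage decrease in the normoxia and hypoxia groups were 3.1 and 6.0% respectively". For the spread it uses a single SD of about 3 percent. It does not mention gender, and does not say whether that SD is pooled over boys and girls or applies within one sex.

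**The concern.** Stratifying by gender balances boys and girls between arms, so the true variance of the treatment difference contains little or no between-gender variance. A model without gender still leaves that variance in its error term. Whenever gender predicts the analysed quantity, the reported standard error therefore exceeds the true one: intervals are too wide and the test rejects less often than its nominal level.

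The two tests named in the plan are not equally exposed.

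- **Main effect of treatment.** This is a between-subject test on each participant's average over visits. A boy-girl difference in the level of the outcome goes into its error term. The primary outcomes are DXA measures (lean mass, fat mass, total, android and gynoid fat percentage) in both sexes at 11 to 15 years, so a difference in level is plausible, although the article gives no figure.
- **Time-by-treatment interaction.** A constant difference in level cancels within each participant. This test is affected only if boys and girls change by different amounts.

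At stake is modest efficiency in a small trial. With 17 analysed per arm the design has little power to spare.

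**Working it through.** **Inputs from the article.** Difference in mean change 6.0 − 3.1 = 2.9 percentage points; SD of change 3; 17 per group for 80% power; 20 per group recruited after 15% dropout (Sample size estimation). Significance level 0.05 (statistical section). I assume a two-sided test.

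**The stated sample size reproduces.** n = 2(1.960 + 0.842)² × 3² / 2.9² = 2 × 7.85 × 9 / 8.41 = 16.8, hence 17 per group, and 17 / 0.85 = 20. The normal approximation gives 80.5% power at 17. The exact noncentral t gives 78.0% at 17 and 84.6% at 20.

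**Assumed gender effect.** The article gives none, so let g be the boy-girl gap in mean change, with half of each arm boys. Holding the total SD at 3:

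- share of variance due to gender: (g²/4) / 9
- within-gender variance: W = 9 − g²/4
- expected error variance without gender: U = W + (g²/4) × 2n/(2n − 2)
- ratio of unadjusted to adjusted standard error: √(U/W)

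For n = 20 per arm, 2n/(2n − 2) = 40/38 = 1.053:

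- g = 0: ratio 1.00
- g = 1: share 3%; W = 8.75; U = 8.75 + 0.25 × 1.053 = 9.01; ratio 1.015
- g = 2: share 11%; W = 8.00; U = 8.00 + 1.00 × 1.053 = 9.05; ratio 1.06
- g = 3: share 25%; W = 6.75; U = 6.75 + 2.25 × 1.053 = 9.12; ratio 1.16

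**Power and type I error.** I simulated the change score with gender balanced across arms, comparing a two-sample t-test with a linear model containing treatment and gender (total SD 3):

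| Gap g | Type I error, unadjusted (20 per arm) | Power at 17 per arm, unadjusted vs adjusted | Power at 20 per arm, unadjusted vs adjusted |
|---|---|---|---|
| 0 | 0.05 | 78 vs 78% | 85 vs 85% |
| 1 | 0.047 | 78 vs 79% | 85 vs 86% |
| 2 | 0.037 | 79 vs 82% | 86 vs 88% |
| 3 | 0.023 | 81 vs 88% | 88 vs 93% |

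Adjusted type I error stays at about 0.05 throughout. Unadjusted power rises slightly with g because the balance itself reduces the true variance of the estimate. The gain from adjustment must be measured against that rising figure, not against a constant 78%.

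**Alternative reading of the SD.** If 3 is the SD within one sex, the total SD grows with g. Unadjusted power for gaps of 1, 2 and 3 points is then about 77, 75 and 70% at 17 per arm (adjusted 78%), and about 84, 82 and 78% at 20 per arm (adjusted 84 to 85%).

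These figures concern change. The article has no data from which to size the effect of level differences on the main-effect test.

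**The case against.** The strongest objection is that the article is merely silent. It names a method and two effects of interest, not a full list of model terms, and nowhere says gender will be left out. Covariates are often left to an analysis plan, and none is shown. Stratified randomisation and repeated measures ANOVA do not contradict each other. This stands to the extent that a reader should not infer that the sponsor has decided to ignore gender. What remains is that the stated treatment analysis does not carry the one factor on which allocation is stratified, and one clause would settle it.

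The second objection is that the harm is conditional. This stands in full. With no gender difference in change the ratio is 1.00 and nothing is lost on the time-by-treatment test. An expected boy-girl difference in body fat level does not by itself damage that test.

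The third objection concerns the margin. The trial recruits 20 per arm, and Attrition and compliance reports 6% dropout in a four-week pilot, so 17 per arm is the planned worst case. With total SD 3, unadjusted power at 20 per arm is about 85% or more for every gap considered. That also stands, subject to the unresolved meaning of the SD. The pilot in Attrition and compliance was all male, and the article does not say whether it is the preliminary experiment behind the sample size.

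**Conclusion.** The point holds as a minor, conditional one. The design stratifies by gender, the stated treatment analysis names no gender term, and if gender is prognostic the reported standard error is too large and the test conservative. For change in fat percentage, the excess is about 0%, 1.5%, 6% or 16% for gaps of 0, 1, 2 or 3 points with total SD 3. The corresponding gain in power from adjustment at 17 per arm is nil, about 1, about 3 or about 8 percentage points. These gaps are assumptions; the article gives no gender difference.

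Three stronger inferences are not supported:

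- **That the unadjusted analysis is invalid.** The estimate is unbiased, and type I error falls rather than rises, so the omission cannot produce spurious positive findings.
- **That the benefit of stratification is wholly lost.** The balance still lowers the true variance of the estimate. What is missing is its reflection in the reported standard error and test.
- **That the stated 80% power is overturned.** At 20 per arm, unadjusted power falls below 80% only if 3 is a within-gender SD and the gap is about 3 points or more.

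**What to change.** State before analysis that gender, as the randomisation stratum, is a between-subject factor in the repeated measures ANOVA, and add a gender-by-time term so that the time-by-treatment test is adjusted too. Adjusting the change-score comparison for gender is equivalent for a single contrast. Apply the same rule to the secondary treatment comparisons.

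The cost is one sentence and about one degree of freedom per term. At 20 per arm, the gender factor takes the between-subject error from 40 − 2 = 38 to 37. Gender-by-time uses one degree of freedom per time contrast, so two over three assessments, taking the within-subject error from 2 × 38 = 76 to 2 × 37 = 74. If gender turns out not to matter, power for the change comparison at 17 per arm moves only from 78.0% to 77.9%. Gender is already recorded, and naming it now prevents adjustment from becoming a post hoc choice.
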